| Enrolled Parent                                                     | Demographics                | Demographic section of the Survey about Caring for Children with Cancer (SCCC), originally developed by study investigators  | Age, gender, race, marital status, number of siblings (of participant child), religion, religiousness, education, zip code.                                                                                                                                                                                                                                                                                                                                                                                                                                                                                                                        |
|                                                                     | Household Material Hardship | Household Material Hardship Survey                                                                                           | Self-report family income, child's health insurance, health literacy, evaluation of household hardship (housing and transportation, utilities, food insecurity, and financial strain)                                                                                                                                                                                                                                                                                                                                                                                                                                                              |

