### 2.6.1. Power considerations

Although the SS is mainly driven by pragmatic considerations (target population is small), power calculations were conducted and indicate that our projected minimal SS of 68 children per group provide sufficient power for both primary and secondary outcomes for clinically meaningful effect sizes. All power calculations presented below were computed with two sample independent one-side tests,  $\alpha=0.05$  unless otherwise specified. For Aims 1 and 2 power estimates are conservative because they only use one observation per subject (average across time) without accounting for the repeated measures within subject.

*Aim 1 HRQoL (primary) and Symptom (secondary) outcomes:* Standard deviations for these outcomes were estimated using data from our PQ study (39 weeks follow up, surveys answered when attending clinic or once a month). For each child, we identified all 16-w periods with  $\geq 6$  surveys and calculated mean PedsQL total and mean PQ-MSAS total scores for each 16-w period. We randomly selected one period per child and estimated the standard deviation of 16-week PedsQL means (SD). Strategy was repeated 10 times and a pooled estimate was calculated. A sample size of 136 children (68 per group) achieves 85% power to detect a 4.4 point increase (MCID) in the mean over 16-w PedsQL Total score (SD for both groups 9.5), and a 95% power to detect a 3-point decrease in mean over 16-w PQ-MSAS total score (SD = 5.3). These power calculations are conservative as they are based on mixed responses coming from parents and children, while in the current proposal responses from different informants will be considered in separate analyses and are expected to have less variability.

*Aim 2 Parental anxiety (S-TAI-State), and depression (CES-D-10) (secondary outcomes):* A sample size of 68 parents per group achieves more than 80% power to detect a moderate to large effect size (Cohen's  $d = 0.43$ ). For example, this effect size would correspond to a difference of 5.2 points in mean S-TAI-State (SD=12.2).

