## 4.3. Statistical methods

### 4.3.1. Overview

All statistical analysis will be conducted on an intention-to-treat basis, i.e. all randomized participants with baseline and at least one post-baseline measurement will be analyzed by original treatment assignment, regardless of adherence. Baseline characteristics will be described and compared between groups using summary measures (e.g. means, medians, rates) and tests selected based on variable distribution. Analyses will be adjusted for factors used in the stratified randomization (center, age group and type of cancer). In addition, if, despite efforts to standardize intervention delivery (section 5.1), we identify substantial differences in fidelity across sites, we will evaluate effect modification by site including the site  $\times$  intervention interaction in the models. The False Discovery Rate criterion will be used to correct for multiple testing in non-planned analyses. Co-I [name] has been the primary biostatistician for all prior PQ analyses and is best suited to head the PQ Response's analysis, along with her team at Deakin University. The PI and Co-I [name] will be part of the leadership team. While all Co-Is will be involved in analysis and manuscript writing, some may take a more prominent role according to their specific expertise (e.g. [name], [name] with aim 2, and [name] with aim 3). DFCI will coordinate data cleaning and programming.

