### 4.3.2. Analysis Plan

#### 4.3.2.1. Comparison of patient-level outcomes (HRQoL and Symptom distress) - Specific Aim 1

The effect of the intervention on child quality of life and symptom burden outcomes (see section 2.4) will be estimated using mixed linear models, with patient as a random effect and group, time (categorical) and group x time interaction and the stratification factors as fixed effects. . The same analysis will be undertaken for the respective domain subscales of PedsQL (physical and psychosocial) and PQ-MSAS (physical and psychological).

#### 4.3.2.2. Comparison of parent-level outcomes (anxiety, depression, HRQoL, and burden) - Specific Aim 2

The same analytical approach described for patient-level outcomes will be followed to analyze parent S-TAI-State, CES-D-10 mean scores and aRSQ symptom-related scores. In S-TAI-State analysis, we will additionally adjust by baseline S-TAI-Trait score. We will also compare depression (CES-D-10  $\geq 10$ ) over time between the two groups using generalized linear mixed models with logit link and binomial distribution. As gender is a predictor of these outcomes, it will be included in these models if imbalanced between arms.

#### 4.3.2.3. Comparison of family activation outcomes - Specific Aim 3

Mixed models, similar to those described for patient-level outcomes, will be fitted to estimate the effect of the intervention on change between week 16 and baseline in Brief COPE active coping, planning, and instrumental support Scores, Total No. of, and No. of different, complementary therapies, and No. of psychosocial clinician encounters over the 16-w study period. Link and distribution for these models will be defined based on the distribution of the outcome variable. We will explore whether change in parent's activation score is modified by parent/child characteristics (e.g. parent's gender, S-TAI-Trait, CES-D-10 scores; and child's diagnosis, among others) including the corresponding interaction terms.

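### Parent gender is named as a predictor of the Aim 2 parent outcomes but is adjusted for only if the arms look imbalanced, which ties the model to observed balance and gives up a little precision

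*Protocol*

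**What the plan says.** Section 4.3.2.2 sets out the Aim 2 models for S-TAI-State, CES-D-10 and the symptom-related stress score, plus a logistic mixed model for depression (CES-D-10 of 10 or more). Its last sentence opens with "As gender is a predictor of these outcomes" and goes on to say that "it will be included in these models if imbalanced between arms". The sentence does not say whose gender. The outcomes are the parent's, and section 4.3.2.3 speaks of "parent's gender, S-TAI-Trait, CES-D-10 scores; and child's diagnosis, among others" as possible effect modifiers, so the parent's gender is the natural reading.

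Four other places bear on this:

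- Table 3 (section 2.5.1) lists gender in the demographic form that the enrolled parent completes at baseline.
- Section 3.1 stratifies randomization by center, age group and type of cancer. Section 4.3.1 adjusts all analyses for the same three factors. Gender is in neither list.
- Section 4.3.2.2 also says of S-TAI-State that "we will additionally adjust by baseline S-TAI-Trait score", with no condition attached.
- Section 4.3.1 plans for baseline characteristics to be "compared between groups using summary measures (e.g. means, medians, rates) and tests selected based on variable distribution".

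**The concern.** The protocol gives prognostic value as its reason for considering gender, and that reason applies whatever the observed split between arms. Making inclusion depend on balance has two consequences.

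First, the Aim 2 model is not settled in advance on this point. Whether gender is in the model is decided by the data, and this would still be so if the statistical analysis plan put a number on what counts as imbalanced.

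Second, when the arms look balanced the known predictor is left out, and the variance it explains stays in the residual.

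The protocol also treats two prognostic baseline variables differently within one paragraph: trait anxiety always enters the S-TAI-State model, while gender enters only on a trigger. Since gender is not a stratification factor, the design does nothing to balance it.

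For the logistic model there is a further point. The odds ratio is non-collapsible, so the conditional treatment effect with gender in the model is a different quantity from the one without it. The rule therefore lets observed balance decide which of the two is reported.

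**Working it through.** **Inputs from the protocol.** Section 2.6.1 gives 68 parents per arm, d = 0.43 for Aim 2, an example of 5.2 points with SD 12.2, and "two sample independent one-side tests" at alpha 0.05. Allocation is 1:1 (section 3.1).

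**Assumptions.** The protocol does not give the share of parents of the minority gender, p, or the gender difference, g, in units of the within-gender SD. I take p = 10-30% and g = 0.2-0.5.

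**Step 1: reproduce the stated power.** Power = Phi(d x sqrt(n/2) - 1.645).

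- For d = 0.43: 0.43 x sqrt(34) = 2.507, less 1.645 = 0.862, so power is 80.6% (80.2% with the noncentral t). This agrees with the stated figure of more than 80%.
- For the example, 5.2/12.2 = 0.426 gives 80.0% (79.6% with the t).

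**Step 2: precision gained by always adjusting.** R-squared = p(1-p)g^2 / (1 + p(1-p)g^2). The standard error is multiplied by sqrt(1 - R-squared), and power becomes Phi(2.507/sqrt(1 - R-squared) - 1.645).

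| p | g | R-squared | SE reduction | Power at d = 0.43 |
|---|---|---|---|---|
| 10% | 0.2 | 0.4% | 0.2% | 80.7% |
| 20% | 0.3 | 1.4% | 0.7% | 81.1% |
| 30% | 0.5 | 5.0% | 2.5% | 82.3% |

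Against 80.6% without adjustment, the gain is 0.1 to 1.7 points.

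**Step 3: simulate the conditional rule.** I used 68 per arm, p = 15% or 30%, g = 0.3 or 0.5, and 20,000 runs per scenario. The residual SD is 1 after gender, so unadjusted power is a little below the step 1 figure. Three triggers were tried as illustrations, since the protocol does not tie imbalance to any one of them.

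- Gender entered in about 5% of runs with a p < 0.05 trigger, about 10% with p < 0.10, and 12-23% with a gap above 10 percentage points. Most trials would therefore omit it.
- Power at d = 0.43 was 78.4-79.7% never adjusting, about 78.6-79.7% under the conditional rule, and 79.6-80.0% always adjusting.
- One-sided type I error (nominal 5%) was 4.6-4.9% under the conditional rule and 4.8-4.9% always adjusting.

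**Step 4: what a chance imbalance does to the estimate.** With a 10-point gap in gender, a 0.4 SD effect and SD 12.2, the unadjusted S-TAI-State difference moves by 0.10 x 0.4 x 12.2 = 0.49 points. For effects of 0.2 to 0.5 SD the shift is 0.24 to 0.61 points. The standard error of the difference is 12.2 x sqrt(2/68) = 2.09 points, so 0.49 points is 0.23 of a standard error (range 0.12 to 0.29).

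**The case against.** The case for leaving the text alone is that very little turns on it. The outcomes are secondary and the primary PedsQL analysis is untouched. Type I error is not inflated, and the power difference is about a point. S-TAI-State is already adjusted for trait anxiety, so to the extent that gender acts through trait anxiety its remaining share is smaller than in the table. The protocol names a single covariate and a single kind of trigger, which limits the choice to two models. All of this stands, and it is why the point is minor.

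A reader might also infer more than the protocol supports:

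- **That the rule biases the result.** Step 4 shows that a 10-point gap could shift S-TAI-State by 0.49 points, which is 9% of the 5.2-point example. That is chance variation well inside the standard error. Randomization keeps the unadjusted estimate unbiased, and the shift ignores the trait adjustment.
- **That such a gap would go unadjusted.** This assumes a significance trigger, which section 4.3.2.2 does not state. An analyst could call 10 points imbalanced and adjust.
- **That the model is chosen after outcomes are seen.** The trigger is the balance of one baseline variable, which can be checked without outcome data. Nothing in the protocol says outcomes are consulted.
- **That the lack of a threshold is itself an error.** A working definition of imbalance is commonly left to the statistical analysis plan, which is not shown.

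What the objection does not answer is the rule itself. Any threshold still leaves a known predictor out of the model when the arms happen to look alike.

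**Conclusion.** The point holds as a minor one about pre-specification and precision in secondary analyses. The rule in section 4.3.2.2 is inferior to fixed adjustment whatever threshold is used, and it does not follow from the protocol's own reason for considering gender.

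Under the assumed ranges, the loss is at most about 2.5% in standard error and 1-2 points of power at d = 0.43, and it may be as little as 0.2% and 0.1 points. These sizes rest on the assumed share of fathers and gender effect, and on the protocol's simplified power calculation with one averaged value per parent. The unconditional form of the trait-anxiety adjustment, and the change of estimand in the logistic model, do not depend on those assumptions.

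The protocol supports no claim of bias, of inflated type I error, or of model choice guided by outcome results.

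**What to change.** In section 4.3.2.2, replace the conditional clause with: *Parent gender will be included as a fixed effect in all Aim 2 models, regardless of observed balance.* Naming the parent also removes the small ambiguity about whose gender is meant. The statistical analysis plan, if it repeats the conditional rule, should be changed to match.

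The cost is one clause and one degree of freedom per model. The variable is already in the baseline form, so no new data are needed.

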### 2.4.2.2. Parent-level outcomes (aims 2 and 3)

**Parent Psychological Distress:** Difference between the two treatment arms in the mean over 16-w of anxiety and depression scores measured on a monthly basis by S-TAI-State and CES-D-10; and on symptom-related stress measured at study entry and at week 16 by *a*RSQ-Stress. Scoring details are presented in section 2.5.1.

**Family activation:** Difference between the two treatment arms in (a) Change in active coping, planning, and instrumental support Brief-COPE scale scores between week 16 and baseline, ordinal variables; (b) Total No. and (c) No. of different complementary therapies used for symptom treatment (reported by parents every 4 weeks), and (d) use of psychosocial services, as measured by total No. of psychosocial clinician encounters documented in the medical record, over the 16-w study period.

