## 2.5. Participant timeline

Participants' timeline is presented in Figure 8. Study participants will be assessed using the PediQUEST web system. At all sites, immediately following consent, the RC will help families register in the system and download the mobile App. All participating parents will be provided with a PQ account, linked to an email of choice. In the case of children aged 2 to 4 years old, only parents will answer PediQUEST Surveys. In the case of children aged 5 to 7 years old, parents and children answer PediQUEST Surveys which are sent to the parent's account; it is expected that parents read the questions out loud to the child. Patients  $\geq 8$  years old will be provided with a PQ account of their own (will need a different email than the one provided by their parent) and will answer PQ-Surveys on their own; in addition, their parents will answer proxy versions (see section 2.5.1). Once a PQ-Survey is assigned, a link is sent by email/notification to the corresponding PQ account owner. In addition, questionnaires can be handed over to participants using the research team tablet for completion, or answered over the phone (administered by the RC) if the participant prefers. PQ Reports will only be available for participants assigned to the intervention arm during the 16 weeks after randomization. After registration, the RC will manually assign the Baseline Packet (30 minutes, online parental survey, preferably answered at the clinic or ward at the time of enrollment). Over a total of 18 weeks (2-week run-in period and 16-weeks post-randomization follow-up), parents and patients  $\geq 5$  years old in both arms will be automatically assigned weekly PediQUEST surveys (10 minutes each, online self-administered surveys answered from any location, provided there is access to internet connection). In addition, parents of both arms will be assigned Monthly Parent Questionnaires evaluating distress, burden, and use of complementary therapies every 4 weeks (15 minutes, online surveys answered independently), beginning at the time of randomization as indicated in Figure 8. Parent Activation Surveys will also be administered at weeks 8 and 16 (the measure at week 8 will be used for an exploratory mediation analysis described in the analysis section 4.3.2.5). Medical records will be abstracted by RCs every four weeks. All patients  $\geq 8$  years old and parents who completed the 16-w follow-up, dropped out, and parents of children who died, and a convenient sample of providers, will be invited to participate in an Exit Interview (in-depth face-to-face or phone interview) administered by the RCs to evaluate study processes, care experience, and intervention fidelity (among those in the intervention arm). There are two points in the timeline with potential for delays. Technical issues, such as troubleshooting access to PediQUEST with participants, or other technical mishaps (which we expect to be rare events), may prolong the run-in period by one or two weeks. In addition, the scheduling of exit interviews will always occur out of the 16-week follow-up period, most frequently within the next week after the last survey is answered, but adapting to the family availability. When a patient dies within the study, the invitation for the exit interview, as explained below, is sent 12-weeks after the death. For these reasons, total enrollment time will be 18 weeks in most cases, but there will be exceptions. This will be explained during the enrollment process.

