|                                                   | Activation             | Brief-COPE                                                           | See above. Measured at weeks 8 (for exploratory analysis see 4.3.2.5) and 16                                                                                                                                                                                                                                                                                                                                                                                                                                                                                  |

|  |  |                                          |                                                                                                                              |
|--|--|------------------------------------------|------------------------------------------------------------------------------------------------------------------------------|
|  |  | Use of complementary therapies checklist | Ad hoc checklist of complementary therapies; parents will report use (yes/no) in past four weeks and reasons for use. |
|--|--|------------------------------------------|------------------------------------------------------------------------------------------------------------------------------|

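### The Brief-COPE effect is estimated as change from baseline to week 16 with no baseline covariate; adjusting for the baseline score would give a more precise comparison at no cost

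*Protocol*

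**What the plan says.** Section 2.4.2.2 defines the outcome as "Change in active coping, planning, and instrumental support Brief-COPE scale scores between week 16 and baseline, ordinal variables". Section 4.3.2.3 keeps that target, the "effect of the intervention on change between week 16 and baseline in Brief COPE active coping, planning, and instrumental support Scores", and gives the model type: "Mixed models, similar to those described for patient-level outcomes, will be fitted". The patient-level model it points to, in 4.3.2.1, is a linear mixed model "with patient as a random effect and group, time (categorical) and group x time interaction and the stratification factors as fixed effects".

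On covariates, section 4.3.1 says: "Analyses will be adjusted for factors used in the stratified randomization (center, age group and type of cancer"). Section 4.3.2.2 adds one baseline score, trait anxiety, for the state-anxiety analysis only. No baseline Brief-COPE covariate is named anywhere.

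Brief-COPE is collected in the baseline packet, before randomization. Table 3 then has it "Measured at weeks 8 (for exploratory analysis see 4.3.2.5) and 16", and section 2.5 explains that "the measure at week 8 will be used for an exploratory mediation analysis described in the analysis section 4.3.2.5". Section 4.3.1 puts in the analysis set every randomized participant who has a baseline value and one or more later values.

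**The concern.** Subtracting the baseline score uses it with a fixed coefficient of 1. Unless baseline and week 16 are almost perfectly correlated, that removes too much and carries baseline measurement noise into the comparison. Letting the data estimate the coefficient avoids this. The baseline score is already collected in both arms, and the analysis set already requires it, so adjustment loses nobody.

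At stake is the precision with which H3 is tested on the three coping scales, in a trial whose size is set by a small population (sections 1.3.1 and 2.6.1).

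A smaller matter is that section 4.3.2.3 does not say how a change from baseline fits into a model with time, group-by-time and a patient random effect. The text allows two readings, and one of them cannot be fitted as written.

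**Working it through.** **The plan's own figure.** Section 2.6.1 gives 80% power for an effect size of 0.5, illustrated as 0.75 points with SD 1.5, using 68 per arm and one-sided alpha 0.05.
- SE of the arm difference = 1.5 × √(2/68) = 0.257.
- Power by the normal approximation is 89.8% one-sided and 83.0% two-sided.
- The stated 80% is not reproduced, but it errs on the cautious side and the point does not depend on it.

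**Variance of the two estimators.** Let s be the SD of the score, equal at both times, and r the baseline-to-week-16 correlation. Per parent:
- change: 2s²(1 − r)
- baseline-adjusted: s²(1 − r²)
- ratio, adjusted to change: (1 + r)/2

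If the SDs differ (s₀ at baseline, s₁ at week 16), change variance minus adjusted variance is (s₀² + s₁² − 2r·s₀·s₁) − s₁²(1 − r²) = (s₀ − r·s₁)². This is never negative. Adjustment is therefore never worse, apart from one degree of freedom for the slope.

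**Size.** The protocol gives no r and does not say whether SD 1.5 belongs to the change or to the score. Both are shown for 0.75 points, 68 per arm, two-sided alpha 0.05. The fourth column is 1 ÷ ratio − 1.

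| Assumed r | Ratio | Variance reduction | Equivalent extra parents | Power, change → adjusted (1.5 is SD of change) | Power, change → adjusted (1.5 is SD of score) |
|---|---|---|---|---|---|
| 0.3 | 0.65 | 35% | 54% | 83.0% → 95.1% | 69.3% → 86.4% |
| 0.5 | 0.75 | 25% | 33% | 83.0% → 92.0% | 83.0% → 92.0% |
| 0.7 | 0.85 | 15% | 18% | 83.0% → 88.5% | 96.4% → 98.3% |

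With 1.5 as the SD of change, the SE falls from 0.257 to 0.207, 0.223 and 0.237.

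**Does the reading of the mixed model matter?** Both readings were fitted to one simulated data set of 136 parents.
- One change score per parent: there are 136 groups of size one. The fit split the variance evenly (0.902 and 0.902) and warned that the Hessian was not positive definite. The random intercept cannot be separated from the residual, and there is no time factor left to fit.
- Baseline and week 16 as repeated rows: the random intercept is identified. The group-by-time estimate is 0.724 (SE 0.230), identical to the simple change-score analysis.
- Week 16 regressed on group and baseline, same data: SE 0.212.

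The loss of precision is the same on both readings.

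**What week 8 adds.** Variance of the week-16 contrast in units of s², with a common baseline mean and equal correlation r between all visits:

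| r | Week 16 missing | Without week 8 | With week 8 | Reduction |
|---|---|---|---|---|
| 0.5 | 0% | 0.02206 | 0.02206 | none |
| 0.5 | 10% | 0.02451 | 0.02424 | 1.1% |
| 0.5 | 20% | 0.02757 | 0.02696 | 2.2% |
| 0.7 | 0% | 0.01500 | 0.01500 | none |
| 0.7 | 10% | 0.01667 | 0.01638 | 1.7% |
| 0.7 | 20% | 0.01875 | 0.01811 | 3.4% |

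**The case against.** The strongest reply is that nothing here is wrong. The change contrast is unbiased under randomization, baseline is used (by subtraction), and power was planned for a score change. If 1.5 is the SD of change, power already exceeds the stated 80%. The outcome is secondary, the gain rests on an assumed r, and a statistical analysis plan commonly settles the covariates of a secondary model. All of that stands, and it is why this is offered as an improvement. It does not remove the point, because the protocol itself fixes change as the target and lists its adjustment factors without the baseline score.

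The objection also rules out several stronger conclusions that a reader might draw:
- **The specified random effect cannot be fitted.** This holds only if one change score per parent is the response. Section 4.3.2.3 can equally mean baseline and week 16 as repeated rows, where the effect on change is the group-by-time term.
- **Leaving out week 8 wastes information.** The protocol assigns week 8 to mediation on purpose. For the week-16 contrast it adds nothing with complete data and little with 10% to 20% missing.
- **Chance baseline imbalance biases the result.** Averaged over randomization it does not. Its effect through regression to the mean is part of the extra variance already counted.
- **Floor and ceiling effects on the 2-to-8 scale condemn change scores.** The documents give no score distribution, and the adjusted analysis uses the same bounded score.

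**Conclusion.** The point holds as an efficiency improvement on a secondary outcome. With a linear model and equal variances, adjusting for baseline lowers the variance by 35%, 25% or 15% at r = 0.3, 0.5 or 0.7. These values of r are assumptions, and the gain shrinks as r rises (10% at r = 0.8). Section 4.3.2.3 leaves the link and distribution to be chosen from the data. Under a non-linear link the ratio need not apply, and the two analyses need not target the same quantity. The documents do not support a claim of bias, of a power shortfall, or of a model that is unfittable on every reading.

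**What to change.** Reword section 4.3.2.3 for Brief-COPE in one of two ways:
- Analyse the week-16 score with group, the baseline score and the stratification factors (ANCOVA, no random effect).
- Model the week-8 and week-16 scores together, with parent as random effect; group, time, group-by-time and the stratification factors as fixed effects; and the baseline score as covariate. Take the week-16 contrast as the Aim 3 result.

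The second form adds little precision, but it matches the analysis set in 4.3.1: a parent with baseline and week 8 only belongs to that set yet has no week-16 change. Week 8 can still serve the mediation analysis.

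If a single change score per parent is kept as the response, drop the patient random effect and the time terms, which are then not identifiable.

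The cost is a few lines of text, with no new data or visits. With a linear model the target, the between-arm difference in change at week 16, stays the same, so section 2.4.2.2 can stand. The change should be made before Brief-COPE results are seen by arm.
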